### 5.4.2 Statistical interim analyses and stopping guidance

There will be no interim analyses performed on this trial.

### 5.4.3 Timing of final analysis

The main analysis is planned when all participants have been to a clinical control 2 years following implantation of ventilation tubes.

### 5.4.4 Timing of the outcome assessments

|                                                                       |       |
|-----------------------------------------------------------------------|-------|
| Clinical assessment and inclusion. Initial evaluation of eligibility. | Day 0 |
| Collection of informed consent to study.                              | Day 0 |

Operative treatment: Installation of tympanostomy tubes.

-

Clinical control and collection of control PROM forms.

Op. + 2 years.

### 5.5 Blinding procedure

Due to the nature of the procedure the patient and surgeon were not blinded. Patients were randomized after inclusion and further follow-up instructions given on the day of the operation. Follow-up controls were either routine through the hospital or as requested by the patients' GP and therefore not blinded. The audiographers responsible for testing were blinded to the patients' allocated group. The data collected will be divided into two groups within our database and assigned a number according to controls through the GP or specialist health care system by a third party. These numbers will be unknown to the outcomes assessor until completion of data analysis. Results from the questionnaires regarding controls performed by the GP or within the specialist health care system will be omitted from the primary analysis to prevent unblinding.

## 6. Statistical principles

### 6.1 Confidence intervals and p-values

All calculated p-values will be 2 sided and compared to a 5% significance level. If a p-value is less than 0.05, the null hypothesis will be discarded. Efficacy estimates for the two alternatives will be presented with two-sided 95% confidence intervals.

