### **Goals**

The overall goal of the study was to find out if controls after drain implantation in the ear drum can be performed as needed by the GP without it having negative consequences for the patient. We also wish to examine if differing follow up after the drain implantation in the ear drum effects the long term effects of the operation.

The primary endpoints are the childrens' hearing two and four years after the operation and secondary endpoints are fluid in the middle ear, number of re-operations, subjective complaints, complication rate and patient satisfaction. Our nullhypothesis is that there is no difference in hearing and other effect variables, and the alternative hypothesis is that there is a difference.

The qualitative part of this study has, as a goal, to collect new information from parents/guardians to children between the ages of 3-10 years who receive implanted middle ear ventilation tubes. The goal is to gather knowledge about guardians expectations with drain treatment and follow-up. Semi-structured interviews of guardians from both follow-up groups will provide new and important information from users of health care services and contribute to overall knowledge base.

We wish to also undergo a health-economic analysis to calculate the course of the patients' treatment/follow up for patients in both the specialist and primary health care systems using data from the Norwegian patient register (NPR) and Control and payment of health refunds (KUHR) now Municipal patient and user register (KPR). This will provide insight into costs for differing levels of healthcare and knowledge about quality of life adjusted life years as a consequence of this intervention.

The results of this study are expected to be published in at least 3 articles which will form part of a PhD degree.

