### **Statistical analysis**

Linear mixed model (LMM) with center as random factor will be used to examine if there is a significant long-term effect (at 2 and 4 years) of treatment (insertion of drain) on hearing level and other audiological and clinical factors. Interaction joints will be included in the statistical model to examine the effect of treatment, measured in the form of change compared to pre-operative measurements, is the difference between patients who receive

follow-up through their GP or hospital. Log transformation of data will be actual if it is relevant to study relative over absolute changes, and transformation of data will be actual if a response variable appears to be skewed. Alternative non-parametric models can be used as needed.

Differences between the two randomization groups (hospital, GP) taking into account severity of complications, number of reoperations and proportion of re-referrals under the follow up period will be examined with the help of chi-squared tests (as a categorical variable) or Mann-Whitney test of differences of the entirety. It will also be actual to compare groups taking into account re-operation rate, and identify riskfactors for recurrence (re-operation), by using different types of survival analysis models, alternatively a logistic regression (if one can not account for time for re-operation).

If there is no significant difference between groups, we will focus on magnitude of differences between groups. With a lack of significant difference we will use a 95% confidence interval for absolute difference around 0 (around 1 for relative difference), but border values in the interval must be less than that which is considered a clinical difference of significance. What these values are will depend on which factors are being analyzed.

The health economic analyses will be performed based on randomization and where follow up has been performed.

In the qualitative portion of the study the transcription of interviews will be done continuously. Multiple researchers belonging to the research group and the project will collaborate to read and analyze the transcript. The analysis method will be adjusted to the data and presented problems.

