### 8.1.2 Statistical analysis

Analyses will be performed according to intention to-treat. Mean +/- SD and summary statistics appropriate for the distribution will be reported for the primary outcome and each of the key secondary outcomes. A linear mixed model (LMM), with the combination of time and treatment as fixed factors (with three levels; 'baseline', 'post-ENT' and 'post-GP') and participant ID as random factor, will be applied to compare mean PTA 2 years after. We will also perform a t-test to compare the mean change in PTA after 2 years between GP controlled patients and those controlled within the specialist health care system.

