## 8.2 Subgroup analyses

Subgroup analysis of the primary endpoint will be conducted for age, gender and severity of hearing loss at inclusion. The groups will be divided into thirds for analysis. Both the complete case set, and the two randomized groups will be divided into thirds according to level of hearing loss or age before subsequent analysis.

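### SAP 6.1 applies its rejection rule to all p-values, with no order, adjustment or exploratory label for secondary endpoints and subgroups

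*Combined protocol and SAP*

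**What the plan says.** SAP 6.1 states: "All calculated p-values will be 2 sided and compared to a 5% significance level". It continues: "If a p-value is less than 0.05, the null hypothesis will be discarded". Nothing in the section limits this to the primary outcome.

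The protocol (Goals) lists the other outcomes: "secondary endpoints are fluid in the middle ear, number of re-operations, subjective complaints, complication rate and patient satisfaction". The same section gives them a hypothesis: "Our nullhypothesis is that there is no difference in hearing and other effect variables, and the alternative hypothesis is that there is a difference". Under Statistical analysis, the protocol says that group differences in complications, re-operations and re-referrals "will be examined with the help of chi-squared tests (as a categorical variable) or Mann-Whitney test". It adds survival or logistic models for re-operation.

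The SAP is more reserved. Section 8.1.2 says that "summary statistics appropriate for the distribution will be reported for the primary outcome and each of the key secondary outcomes", but it neither lists the key secondary outcomes nor names a test for them. Section 8.2 says: "Subgroup analysis of the primary endpoint will be conducted for age, gender and severity of hearing loss at inclusion". It describes a division into thirds, and gives no test, interaction term or rule for interpretation.

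Neither document contains a hierarchy, an alpha split, a gatekeeping step or an exploratory label. The SAP's table of contents shows no section on multiplicity.

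**The concern.** A rule that covers all p-values also covers the tests that the protocol plans on secondary outcomes, which the SAP does not withdraw, and any p-value produced in the subgroup analyses. Read literally, a p-value of 0.04 for one complication measure or one age third is a rejected null hypothesis.

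The trial asks whether GP follow-up is safe and sufficient, and the protocol (Consequences) expects the answer to influence practice in either direction. A chance finding in one stratum or on one secondary outcome could therefore be presented, with the SAP's support, as an established difference between GP and hospital follow-up.

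**Working it through.** **The plan's own figure.** The documents state no family-wise error rate. The 5% level is tied to a sample size for one comparison (SAP 5.3: difference 5 dB, SD 10 dB, two-sided 5%, power 95%):

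n per group = 2 × (1.960 + 1.645)² × (10/5)² ≈ 104.

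The t-test version gives 104.9, which is the plan's 105. The design therefore spends its full 5% on the primary comparison alone.

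**Counting the tests.** The protocol names five secondary endpoints. SAP 8.2 gives no count of subgroup tests. Taking three age thirds, three thirds of hearing loss and two genders gives 3 + 3 + 2 = 8 strata. Together that is 13. These counts are assumptions. Section 8.2 divides both the complete case set and the two randomized groups, so more than one set of cut points is possible.

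**Independent tests, all nulls true.** P(at least one p < 0.05) = 1 − 0.95^k:

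- k = 5: 22.6%
- k = 8: 33.7%
- k = 13: 48.7%
- k = 14: 51.2%

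**Allowing for dependence.** The tests are not independent. Each child belongs to one age third, one hearing-loss third and one gender, so strata of different factors overlap. Thirds of the same factor share no children, so one common correlation across all 13 tests would be wrong. I simulated 270 children (135 per group) with no effect, 20,000 trials per row. There was one primary outcome analysed in the eight strata, and five secondary outcomes. All six outcomes had the same assumed pairwise correlation, and the three stratifying factors were independent of each other. Each test was a two-sided 5% t-test.

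| Correlation between outcomes | Primary test | Any of 5 secondaries | Any of 8 strata | Any of 13 |
|---|---|---|---|---|
| 0 | 4.9% | 22.6% | 29.0% | 44.9% |
| 0.3 | 5.0% | 21.0% | 29.3% | 43.1% |
| 0.5 | 5.1% | 18.3% | 29.1% | 39.5% |
| 0.7 | 4.6% | 14.6% | 28.6% | 35.3% |

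The primary test stays at about 5% throughout. The inflation lies entirely in the other tests.

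**What rejection means.** In SAP 5.4.1 the null hypothesis is that GP follow-up gives poorer PTA results, and the alternative is non-inferiority. The next paragraph says that rejecting the null means that a difference is claimed. In the protocol the null is no difference. The same p-value under 6.1 could thus be read as non-inferiority or as a difference, so the rule is unclear for the primary outcome too.

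**The case against.** The strongest reply is that the plan is more restrained than 6.1 read alone suggests. A reader might infer that every secondary endpoint and subgroup will be tested and decided at 5%. The SAP does not say so: 8.1.2 promises only summary statistics for key secondary outcomes, and 8.2 names no test. The commitment to test secondary outcomes comes from the protocol.

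A reader might also infer that such results have the same standing as the primary. The documents do not support that. They separate primary from secondary endpoints, and the only explicit rule for claiming a difference or superiority (SAP 5.4.1) concerns change in PTA. Nor do they support saying that a false difference is more likely than not. The 13 countable tests stay below 50% even under independence, and passing it takes 14 or more near-independent tests. Adding 4-year outcomes would raise the count, but the SAP's analysis and schedule stop at 2 years.

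All of this stands, and it limits the point. It does not remove it. The protocol's tests have not been withdrawn, 6.1 would govern their p-values, and the word secondary does not exempt an outcome from a rule written for all p-values. The protocol also makes significance the first step of interpretation, since it turns to the size of the difference and its confidence interval only when no significant difference is found.

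**Conclusion.** The gap is real and moderate in size. Any p-value calculated outside the primary comparison falls under an unrestricted rejection rule with no order, adjustment or exploratory label. If all nulls are true, the chance of at least one false rejection is about three to nine times the nominal 5%, depending on which family is counted: the lowest simulated figure is 14.6% (14.6/5 ≈ 2.9) and the highest 44.9% (44.9/5 ≈ 9.0).

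These figures rest on five secondary outcomes at one time point, eight strata, correlations from 0 to 0.7 between outcomes, and 135 analysed per group. The documents fix none of the correlations and leave the number of tests open. This is a weakness in labelling and interpretation. It does not invalidate the primary analysis.

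**What to change.** 1. Limit the rejection rule in SAP 6.1 to the comparison of 2-year change in PTA defined in 5.4.1. Say which analysis carries the claim, because 8.1.2 gives both a mixed model and a t-test.
2. Reconcile 5.4.1, so that its null hypothesis and the conclusion drawn from rejecting it agree.
3. List the secondary outcomes in the SAP and add, for example: *Secondary endpoints and subgroup analyses are exploratory. They are reported as estimates with 95% confidence intervals; p-values are nominal and no hypothesis is rejected on them.* If a confirmatory secondary claim is wanted, name one endpoint and test it at 5% only after the primary succeeds.
4. Assess each subgroup factor by a treatment-by-subgroup interaction instead of separate tests within thirds. Three interaction tests at 5% would still carry up to about 1 − 0.95³ = 14% if independent, so they stay exploratory.
5. Report complication rate as a safety outcome with its estimate and confidence interval, and state that non-significance will not be taken as evidence of safety.

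The cost is a few sentences, with no change to the sample size or the primary alpha. The downside is that a nominally significant secondary or subgroup result can no longer be presented as confirmed. A formal adjustment would cost more. With 135 × 0.8 = 108 evaluable per group (20% dropout assumed) and a standardized effect of 0.5, a Bonferroni level of 0.05/5 = 0.01 lowers the power of each secondary test from 95.7% to 86.4%.

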### 6.2 Adherence and protocol deviations

Upon drafting of the protocol a seventh hospital was to be included. Due to problems involving the inclusion of patients they removed themselves from the study without contributing to the data set. In addition to this our initial goal was to include 400 patients. However, due to a drastic reduction in the implantation of tympanostomy tubes under the Covid-19 pandemic this was reassessed, and that number was reduced to 135 patients per group. Cases which do not adhere to the study protocol will be excluded.

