In Norway children are primarily followed up in hospital or by Ear-Nose-Throat (ENT) doctors in private practice who have operated on them, with time intervals which vary from hospital to hospital. This often occurs less often than that which is recommended by guidelines. Many hospitals have problems completing these controls within the planned timeframe, due to long wait-lists and lack of capacity. Even though most hospitals still control all children who undergo drain operations themselves, St. Olavs Hospital implemented a change in 2007. From then controls of those children assumed to be the most healthy who received drains were delegated to their GP, while children with serious

hearing loss or other medical syndromes were controlled at hospital. GP controls were 6 and 18 months after the operation and guardians would have to order the control appointments for themselves. This follow up was evaluated through a retrospective study that did not find any difference in hearing, middle ear fluid or ear complaints 2 years after the operation (14). Another study on the same material showed that children came to GP controls even though they were not called in, but many children were controlled by both GP and ENT regardless of where controls were originally planned (15).

There were, however, many limitations in this study. These included the small amount of material, the lack of randomization and that complications were not controlled over and above re-operations. In addition to this many GPs were unsure of how they should perform these controls (unpublished, own data). We would therefore like to perform a new and larger study to give more strength to recommendations nationally and internationally on the follow up of children after the implantation of drains. We will randomize children into two groups: ENT follow up and GP follow up as needed.

A potential benefit of follow up after intervention in hospital, may be the specialized equipment required for follow-up, while a potential benefit of GP controls may be short travel time and easier accessibility. As of now we know little about parents/guardians expectations to the intervention and follow-up as well as how this is experienced. We would therefore like to perform a qualitative part to this study.

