## 5. Trial methods

### 5.1 Trial design

This is a multicenter randomized non-inferiority study involving six centers in Norway and organized through St. Olavs Hospital, Trondheim, Norway. Patients were included through Gjøvik hospital, Stavanger University Hospital, hospitals in Ålesund and Molde as well as a private practice in Kristiansund. An initial assessment of eligibility was performed through the out-patient ENT clinic upon further referral for operative implantation of tympanostomy tube(s). The surgical procedure was performed at one of the aforementioned hospitals.

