### 5.3 Sample size

The sample size was calculated prior to inclusion by a statistician. Hearing thresholds are determined in 5 dB steps and equality in PTA 2 years after surgery (primary endpoint) was

therefore defined as  $< 5$  dB (5 dB as equivalence margin). To avoid an incorrect conclusion of ‘no difference’ between the groups (type II error), the power of the tests for detecting a difference of  $\geq 5$  dB must be high ( $\geq 95\%$ , error margin  $< 5\%$ ). Thus, with a power of 95% and a significance level of 5% (two-sided test), 105 participants are needed in each group to be able to detect an absolute difference in mean PTA between the groups of  $\geq 5$  dB (SD 10 dB) in each group based on the results of our previous study. 15% was added to mitigate a potential skew distribution of hearing level, and an additional 20% to account for potential dropouts, we are left with a sample size of 145 participants in each group. To maintain power in an analysis stratified for six study centers (five additional parameters in model), the total sample size must be increased by at least 50 participants, applying the general rule of thumb of at least 10 cases per parameter. If we assume that the 50 participants are evenly distributed in the two randomization groups, this leaves us with a sample size of at least 170 participants in each group. We initially planned to truncate up to 200 participants in each group to maintain power in case of a higher dropout rate. However, during the pandemic the surgery rate in Norway dropped dramatically, and with it our inclusion rate. After a preliminary assessment of our drop-out rate and recalculation by the project’s statistician, it was determined that 135 participants in each group would be sufficient.

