### 6.3 Analysis groups

- All randomized patients (All randomized patients, including those lost to follow-up.)
- Full analysis set (All patients which were randomized and treated.)
- Complete case set (All data present at both baseline and control)

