## 7. Trial sample

### 7.1 Screening data, eligibility and recruitment

The total number of included patients and reasons for non-completion will be summarized and tabulated. A trial profile flow diagram will be used to summarize the number of patients who were:

- Included at initial evaluation
- Eligible at initial evaluation and underwent installation of tympanostomy tubes.
- Received randomized allocation.

- Lost to follow-up.
- Randomized and included in primary analysis.
- Randomized and excluded from primary analysis.

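### The exclusion of non-adherent cases in SAP 6.2 contradicts intention-to-treat in 8.1.2, is undefined, and can bias the comparison in either direction

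*Combined protocol and SAP*

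**What the plan says.** SAP 6.2, after describing the withdrawn hospital and the reduced recruitment target, ends with an unqualified rule: "Cases which do not adhere to the study protocol will be excluded". It does not say what non-adherence is or which analysis the rule applies to.

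SAP 8.1.2 opens the primary analysis with: "Analyses will be performed according to intention to-treat".

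SAP 6.3 lists three sets: all randomised patients, a full analysis set (randomised and treated) and a complete case set. None is per-protocol, and none is named as the set for the primary analysis. SAP 7.1 gives the flow diagram a category "Randomized and excluded from primary analysis".

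The design statement in SAP 5.1 reads "This is a multicenter randomized non-inferiority study involving six centers in Norway", and 5.3 gives "5 dB as equivalence margin".

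On where care takes place:
- Protocol, Design and procedure: the hospital arm has six-monthly controls while clinically needed; the GP arm is seen only as required.
- Protocol, Ethics, and SAP 9: the GP may refer a child on to hospital or ENT when problems arise.
- Protocol, Background: in the earlier retrospective cohort, "many children were controlled by both GP and ENT regardless of where controls were originally planned".

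**The concern.** Intention-to-treat keeps every randomised child in the allocated arm; the rule in 6.2 removes some of them for what happened afterwards. An analyst cannot do both, and the SAP does not say which prevails. Because non-adherence has no definition, the choice of whom to remove would be made during the analysis.

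The randomised intervention is the place and pattern of follow-up, so one natural reading of non-adherence is follow-up in the other setting. Contact in the GP arm is prompted by symptoms, so attendance at ENT can be related to hearing, which is the outcome. If such children were counted as non-adherent, the GP arm would lose some of its worst results and the comparison would lean towards non-inferiority. The same sentence can also remove hospital-arm children who miss controls, with a different effect. At stake is whether the primary non-inferiority conclusion rests on the randomised comparison.

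**Working it through.** **1. Can the text be reconciled?** The exclusion would be harmless if it applied only to a sensitivity analysis, but 6.3 offers no per-protocol set to hold it. It would also be harmless if another section overrode it, but 8.1.2 does not mention it and 7.1 anticipates exclusions from the primary analysis. The conflict stands on the text alone.

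**2. The plan's own sample size.** SAP 5.3 says that "with a power of 95% and a significance level of 5% (two-sided test), 105 participants are needed in each group", for a 5 dB difference and SD 10 dB.

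n = 2 × (1.960 + 1.645)² × 10² / 5² = 103.96, so 104 per group. This agrees with the stated 105.

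**3. Number analysed.** The final target is 135 per group (SAP 5.3, 6.2). The drop-out rate behind that figure is not given, so I assume the 20% allowed for in 5.3: 135 × 0.8 = 108 per group.

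**4. Bias formula.** Let f be the share of an arm excluded and g the amount in dB by which the excluded children are worse than those kept. The mean of the whole arm equals the mean of those kept plus f × g. Hence

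bias in favour of GP = f(GP) × g(GP) − f(hospital) × g(hospital).

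**5. Effect on the conclusion.** Assume non-inferiority is claimed when the upper 95% confidence limit for GP minus hospital lies below 5 dB. At a true deficit of 5 dB, with exclusion in the GP arm only,

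false non-inferiority rate = Φ(f × g / SE − 1.96), with SE = 10 × √(1/[108(1 − f)] + 1/108).

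SE is 1.398 for f = 10% and 1.443 for f = 20%. Both f and g are assumptions.

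| f (GP arm only) | g | Bias towards GP | False non-inferiority rate |
|---|---|---|---|
| any | 0 dB | 0 | 2.5% |
| 10% | 5 dB | 0.5 dB | 5.5% |
| 10% | 10 dB | 1.0 dB | 10.7% |
| 20% | 5 dB | 1.0 dB | 10.3% |
| 20% | 10 dB | 2.0 dB | 28.3% |

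For scale, I simulated an outcome with SD 10 dB and excluded the 10-20% with the highest tendency to be excluded. A correlation of 0.2 between that tendency and poor outcome gives g of 3.5-3.9 dB; 0.4 gives 7.0-7.8 dB; 0.6 gives 10.5-11.7 dB. The upper row of assumptions therefore needs fairly strong selection.

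**6. Other patterns.**
- Both arms lose equal shares with the same g: bias is zero and the rate stays 2.5%.
- Hospital arm only, f = 20%, g = 10 dB: bias is 2 dB against GP. With no true difference, the chance of showing non-inferiority is Φ(3/1.443 − 1.96), about 55%. With the same numbers and no bias it is Φ(5/1.443 − 1.96), about 93%.
- Hospital-arm children excluded because they were well and skipped controls: g(hospital) is negative, so the bias is again towards GP.

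**7. Precision.** Power for 5 dB is Φ(5/[10√(2/n)] − 1.96): 95.7% at n = 108 and 93.0% at n = 94.5 (30% total loss in each arm). Lost power is a minor matter.

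**The case against.** A reader might infer that the rule will remove GP-arm children who went to ENT because they did badly, and so will favour non-inferiority. The documents do not support that as a prediction:

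- Referral from GP to hospital or ENT is part of the planned pathway (Protocol, Ethics; SAP 9). On a plain reading, a GP-arm child referred for a complication has adhered. The mechanism needs that child to be classed otherwise, or concerns children who bypass the GP.
- The GP arm has no visit schedule to miss; the hospital arm does. The Background section says many hospitals struggle to complete controls on time. Exclusions could fall mainly on the hospital arm.
- The crossover remark in the Background describes a retrospective, non-randomised cohort with planned GP controls at 6 and 18 months. It covers both settings and gives neither a rate nor a reason.
- SAP 5.5 keeps questionnaire results on where controls took place out of the primary analysis, and 8.1.3 keeps baseline data of children lost to follow-up in the mixed model. Both suggest intention-to-treat was the working intention.

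All of this stands against a claimed direction. It does not remove the contradiction. The SAP nowhere says that a referred child is adherent, and 5.5 does not rule out exclusion on journal data, which the protocol allows to be reviewed at 2 and 4 years. A reader might also infer that the exclusion leaves the trial too small. It does not: 20% off 135 is 108, still above the base requirement of 105.

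**Conclusion.** The contradiction between 6.2 and 8.1.2 is certain, and as written the primary analysis population is undetermined. This must be settled before the analysis, because following 6.2 would break the randomised comparison.

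The direction and size of any bias are not established. Under the assumption that 10-20% of the GP arm alone is excluded and hears 5-10 dB worse than those kept, the bias is 0.5-2 dB, or 10-40% of the 5 dB margin, and the false non-inferiority rate rises from 2.5% to about 5-28%. Under other patterns equally open on the text it is zero or runs the other way. These figures also assume SD 10 dB, 108 analysable children per arm before exclusion, and a confidence limit compared with 5 dB. They show what the wording permits, not what is expected to happen.

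**What to change.** - Remove the exclusion in 6.2 from the primary analysis.
- In 6.3 and 8.1.2, name all randomised children, analysed in their allocated arm, as the primary set. Treat a missing two-year audiogram as missing data under 8.1.3, not as non-adherence.
- Define non-adherence before the group codes are opened, for both arms. State that referral from GP to ENT under the documented pathway (Protocol, Ethics; SAP 9) is not a deviation.
- Use the exclusion only in a named, supportive per-protocol analysis. It should address crossover between settings, which can dilute differences under intention-to-treat and so matters in a non-inferiority trial. Criteria limited to eligibility, consent and an available audiogram would nearly repeat the complete case set. Report it beside the primary result with numbers and reasons for exclusion by arm, since it carries the selection risk described above.
- Align the flow-diagram category in 7.1 with these definitions.

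The cost is SAP wording and one supportive analysis.
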